### Data management {19}

Wherever possible, study data collected during clinic visits will be recorded directly into an electronic data capture system (REDCap). The data capture system will be programmed with quality control measures including range checks for quantitative variables. When direct data entry is not practical or is not available, the data will be recorded in a source document and will be transcribed into the electronic data capture system using double data entry within a reasonable timeframe. All electronic and nonelectronic documents and forms will be kept securely. Full details of data management procedures are provided in the study data management plan.

### Confidentiality {27}

All data will be encrypted and stored on password-protected servers, which have multifactor authentication activated to ensure secure access control. Each participant will be assigned a unique project identity number (ID) for capturing and storing their data. Personal identifiers will not be stored in the study data set, and all computers will be equipped with antivirus software and security passwords. Participant contact information will be kept separately from project documentation. While the study is in progress, study-related forms will be maintained in locked cabinets, with access restricted to authorised personnel only. Upon study conclusion, these documents will be digitised, indexed, and stored indefinitely on the central server. The original paper documents will be destroyed.

### Plans for collection, laboratory evaluation, and storage of biological specimens for genetic or molecular analysis in this trial/future use {33}

Samples will be collected according to the study laboratory manual and standard operating procedures. At each visit, DBS will be taken and stored for future analysis of drug levels and HIV viral load. The results of the dry blood spot analysis will not be given directly to the participants or clinic study staff but to the study team for the analysis. Furthermore, for individuals who acquire HIV during the study, blood will be taken for analysis including HIV viral load, resistance testing, drug levels, and storage for future use.

## Statistical methods

### Statistical methods for primary and secondary outcomes {20a}

The demographic, behavioural, and clinical characteristics of the two enrolled groups at baseline will be summarised, both overall and stratified by setting. All analyses will be done by intention to treat. No formal adjustment for multiplicity is planned for the co-primary effectiveness and implementation outcomes as the framework for effectiveness is superiority and that for implementation is exploratory.

For the primary user effectiveness outcome (persistence on PrEP during the randomised period), the odds ratio for persistence on PrEP comparing the two trial arms and a corresponding 95% confidence interval (CI), and *p*-value, will be generated using logistic regression, adjusting for setting (as randomisation is stratified by setting). The same approach will be used for binary secondary outcomes. For persistence during the full follow-up period, which is a multinomial outcome, multinomial logistic regression will be used, adjusted for setting.

For primary implementation outcomes, the odds ratio for uptake of PrEP comparing the two trial arms and a corresponding 95% CI, and *p*-value, will be generated using logistic regression, adjusting for setting (as randomisation is stratified by setting). Similarly, an odds ratio for the proportion who choose injectable compared to oral PrEP and a corresponding 95% CI, and *p*-value, will be generated using logistic regression, adjusting for setting.

A full statistical analysis plan will be finalised before database lock and will include sensitivity analyses to assess the impact of each element of the primary effectiveness outcome (which is a composite outcome) on study findings and to investigate a more flexible visit window for PrEP persistence.

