**Intervention**											
CAB-LA injection			X	X	X		X	X			
Oral PrEP dispensed			X	X		X		X			
**Assessments**^**2**^											
Locator information	X			X		X			X	X	
Demographics	X										
Risk and mobility (short CRF)	X			X	X	X	X	X	X	X	
Risk and mobility (Long CRF)	X								X		X
PrEP adherence				X	X	X	X	X	X	X	X
Adverse events			X	X	X	X	X	X	X	X	X
IDIs				X		X	X		X	X	X
FGDs				X					X		X
Surveys	X								X		X
HIV test	X			X	X	X	X	X	X	X	X
STI screen	X								X		
DBS	X			X	X	X	X	X	X	X	X
Blood pressure	X				X	X			X	X	X
BMI	X				X	X			X	X	X
CrCl if ≥ 30 years	X										
HepBsAg	X										

^1^Visit schedule for choice phase is dependent on choice of PrEP made at month 9 and at each subsequent visit. ^2^Done at visits corresponding to the intervention received by the participant; *CAB-LA*, long-acting injectable cabotegravir; *PrEP*, preexposoure prophylaxis; *CRF*, case report form; *IDIs*, Iin-depth interviews; *FGDs*, focus-group discussions; *HIV*, human immunodeficiency virus; *STI*, sexually transmitted infection; *DBS*, dried blood spot; *BMI*, body mass index; *CrCl*, creatinine clearance; *HepBsAg*, hepatitis B surface antigen

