### Sample size {14}

The planned enrolment sample size of 400 participants (randomised) will allow 80% power to detect an absolute difference of 11% in persistence between trial arms at a 5% significance level, assuming 80% persistence in the lower persistence arm [40] (and 91% persistence in the higher persistence arm) and allowing for 20% lack of ascertainment of persistence, for example, due to medical ineligibility to receive the randomised intervention or death. If the persistence in the lower persistence arm is lower, at 60% [41], then we will have 80% power to detect an absolute difference of 15% (i.e. 60% versus 75% persistence). Sample size is calculated using standard methods for comparing two proportions and implemented using the “power two proportions” command in STATA.

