### Masaka, Uganda

Recruitment efforts will mainly focus on landing sites around the shores of Lake Victoria in Masaka District. These fishing communities have a high HIV burden that is attributed to several factors, including high mobility, sex work, relatively young populations with disposable daily income, and inadequate health services. People in these communities frequently move between different landing sites and islands, with up to 47% of men and 25% of women reporting being away from home for at least 2 days each month. This mobility is mainly driven by the seasonal fish catch. Previous studies have highlighted that such high mobility can limit access to health services, increase HIV infection risk, and underscore the need for tailored HIV prevention interventions that account for these mobility patterns [39, 42]. The Mobile Men study has been designed to address these challenges.

The study team will work with local leaders and members of Village Health Teams and via community HIV testing services to identify potential participants from places of entertainment (such as lodges/guest houses, bars) and from their homes. Detailed locator information, including addresses, telephone contacts, and next-of-kin details, will be collected to facilitate effective phone and/or physical tracing during the follow-up phase of the study.

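### The primary persistence model adjusts for setting only; this is valid and meets the stated power, but naming age and baseline mobility as covariates could add a modest amount of power at little cost

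*Protocol article*

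**What the plan says.** Statistical methods for primary and secondary outcomes {20a} specifies logistic regression giving an odds ratio, 95% CI and p-value for persistence, "adjusting for setting (as randomisation is stratified by setting". No other covariate is named. The sensitivity analyses promised for the SAP concern the elements of the composite outcome and the visit windows, not covariates.

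Sequence generation {16a} stratifies the 1:1 randomisation by setting (three groups), so model and design agree.

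Table 1 places demographics and the row beginning "Risk and mobility (Long CRF" at enrolment. The section on the quantitative survey lists age and mobility patterns among its items.

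The recruitment text for Masaka, Uganda, reports from previous studies that "such high mobility can limit access to health services".

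Sample size {14} claims that 400 randomised men "will allow 80% power to detect an absolute difference of 11% in persistence between trial arms". Its inputs are a significance level of 5%, a persistence of 80% in whichever arm does worse, and a 20% allowance for men whose persistence cannot be ascertained. A second scenario is "60% versus 75% persistence". The method is a plain comparison of two proportions with no covariates.

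**The concern.** Under Outcomes {12}, a man in the CAB-LA arm is persistent only if every injection falls within 7 days of schedule. A man in the oral arm must attend the 3-monthly visits, receive enough supply and have detectable TFV-DP. Under {20c}, loss to follow-up counts as non-persistence. Time away from home therefore bears on much of the outcome in both arms, and the protocol's own rationale is that mobile men find services harder to reach.

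When a baseline variable predicts a binary outcome, including it in the logistic model raises the power of the treatment test and accounts for chance imbalance in that variable. Recruitment has closed (Trial status), so the sample size can no longer be raised, and the main scenario was sized with no margin. At stake is a possible small increase in power from data already collected. The validity of the planned analysis is not in question.

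**Working it through.** **1. Reproduce the plan's figure.** Inputs from Sample size {14}: 80% v 91%, 5% significance (sidedness not stated; two-sided assumed), 80% power, 20% not ascertained.

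n per arm = [1.960 × √(2p̄(1−p̄)) + 0.842 × √(p₁(1−p₁) + p₂(1−p₂))]² / (p₂−p₁)², where p̄ is the mean of p₁ and p₂.

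- 80% v 91%: p̄ = 0.855. The two terms are 0.976 and 0.414, so n = (1.390)² / 0.0121 = 159.7, that is 160 per arm. Then 320 / 0.80 = 400, the stated figure. Power at 160 per arm is 80.1%.
- 60% v 75%: n = 152 per arm, and 304 / 0.80 = 380. Power at 160 per arm is 82.0%, and the detectable difference is 14.6 points, consistent with the stated 15%.
- A continuity correction would need 445 in total, and a one-sided test only 126 per arm, so the uncorrected two-sided formula is the one used.

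**2. Does the setting-only model deliver this?** Yes. In simulation it gives about 80% to 81% power for 80% v 91%, and about 81% to 83% for 60% v 75%.

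**3. What would covariates add?** The simulation used 8,000 trials per cell, 160 per arm, three equal settings with no setting effect, and a two-sided Wald test. It compared arm + setting with arm + setting + one standardised baseline score, holding the marginal rates at the protocol's values. The document gives no prognostic strength, so the odds ratio per SD of the score is an assumption and is varied.

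| OR per SD | AUC | 80% v 91%: setting only → plus score | 60% v 75%: setting only → plus score |
|---|---|---|---|
| 1.00 | 0.50 | 79.7 → 79.5 | 82.7 → 82.7 |
| 1.22 | 0.56 | 80.6 → 80.6 | 82.6 → 82.5 |
| 1.49 | 0.61 | 80.4 → 81.1 | 82.6 → 83.5 |
| 1.82 | 0.66 | 81.0 → 82.5 | 82.0 → 84.3 |
| 2.23 | 0.70 | 80.1 → 82.7 | 81.4 → 85.6 |
| 2.72 | 0.74 | 81.4 → 85.2 | 81.3 → 88.0 |
| 4.48 | 0.81–0.82 | 80.7 → 88.8 | 83.0 → 92.5 |

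Monte Carlo standard error per power figure is √(0.8 × 0.2 / 8000), about 0.4 points. A separate run (6,000 trials per cell, likelihood-ratio test) agrees: at log-odds 0.4 per SD (OR 1.49), 80.3 → 81.4 and 82.0 → 83.5; at log-odds 1.0 (OR 2.72), 80.9 → 84.8 and 82.3 → 88.8.

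**4. Can the model carry two more terms?** In the main scenario the expected number of non-persistent men is 160 × 0.20 + 160 × 0.09 = 32 + 14.4, about 46. Arm, two setting terms, age and mobility, each entered as one term, make five coefficients, or about 9 events per coefficient. Two single-term covariates are manageable; a long list is not.

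**The case against.** The strongest case is that nothing here is wrong. Adjusting for the stratification factor is standard, contradicts nothing in the document and meets the power claim. That stands in full.

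The evidence that mobility is prognostic is also indirect. The Masaka sentence concerns access to services in the fishing communities, not PrEP persistence in this trial, and the text goes on to say that the study was designed to address these challenges. Every participant is mobile by eligibility, and setting already absorbs differences between sites. These points lower the likely gain but do not remove it. Entry needs only one night away for work in 6 months, and the Buffalo City site alone recruits roadside casual labourers, migrant workers and truck drivers, so mobility can still vary widely within a setting.

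The base of 160 per arm is probably conservative, because men lost to follow-up stay in the analysis as non-persistent and only medical discontinuations are excluded. If 5% were excluded (an assumption), 190 per arm would give z = (0.11 × √190 − 0.976) / 0.492 = 1.10, or about 86% power for 80% v 91% with no covariates. This stands and makes the extra power less needed.

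Timing is a fair objection. Recruitment ended on 8 November 2024, so the 9-month randomised period ended around August 2025, and {17a} says the analysis is unblinded. Replacing a published primary model late could look data-driven. The fix has to depend on what has been seen.

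A reader might infer that the trial forgoes a known 5 points or more of power, or that setting-only adjustment is biased or leaves the trial underpowered. The documents support none of these. Gains of that size need an AUC well above 0.70 in the main scenario, no passage gives any association between age or mobility and persistence, and chance imbalance is already reflected in the planned confidence interval.

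**Conclusion.** The point holds as an optional improvement of low severity. The plan fixes a valid model that meets its stated power and does not use two baseline variables that are already collected and plausibly prognostic. For an assumed AUC of 0.50 to 0.70, the gain at 160 per arm is about 0 to 3 points for 80% v 91% and 0 to 4 points for 60% v 75%. With no prognostic value the change is within simulation error.

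The size rests on an assumed prognostic strength, on one score acting equally in both arms, and on 160 analysed per arm. The equal-effect assumption is doubtful: the outcome is not attendance alone, since the oral arm also needs sufficient supply and detectable TFV-DP, so age or mobility may predict it differently by arm.

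**What to change.** In the SAP, before any outcome data by arm are examined:

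- Name age and baseline mobility, as recorded on the enrolment risk-and-mobility CRF, as covariates alongside setting in the persistence model, and state their functional form. The article does not show which mobility quantity is recorded (nights away, for example), so the variable must be chosen from the CRF itself.
- Report a standardised risk difference with the odds ratio. This also matches the absolute-difference scale of the sample size statement.
- Keep the published setting-only model as a sensitivity analysis.
- Give a rule for missing covariate values. Under {20c}, complete case analysis applies when missing data do not exceed 10%, which would drop randomised men merely for lacking a baseline value.

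If outcome data by arm have already been seen, leave the published model as primary and make the adjusted model the supporting analysis.

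The cost is SAP wording and no new data. The downside is that the adjusted odds ratio becomes conditional on more variables, so it is not directly comparable with the setting-only odds ratio; the standardised risk difference deals with this.

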### Interim analyses {21b}

No formal interim analyses are planned. Interim data on protocol adherence and safety will be reviewed by an Independent Data Monitoring Committee (IDMC), but no formal stopping guidelines are planned.

### Methods for additional analyses (e.g. subgroup analyses) {20b}

Subgroup analyses by study setting will be done to determine whether differences between trial arms are consistent across settings. These will be assessed by stratifying analyses by setting and testing for interaction.

### Methods in analysis to handle protocol non-adherence and any statistical methods to handle missing data {20c}

The primary analysis population will be all randomised participants, regardless of protocol adherence or use of PrEP, with the exception that participants who are discontinued from receiving their allocated PrEP for medical reasons will not be included in the primary user effectiveness outcome analyses. No per-protocol analyses are planned. Participants who are lost to follow-up will be included in primary user effectiveness outcome analyses, as they will be considered non-persistent on PrEP. If the proportion of participants with missing data is > 10%, then multiple imputation will be investigated; otherwise, complete case analysis only will be used.

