### Outcomes {12}

The trial will have two co-primary outcomes:

User effectiveness co-primary outcome: This will assess persistent use of PrEP during the randomised period and throughout the full follow-up period. Persistent use of PrEP during the randomised period will be defined as a binary outcome. Participants randomised to the CAB-LA arm who receive all injections as per schedule (initial injection at month 0, followed by injections at months 1, 3, 5, and 7, with an acceptable window of ±7 days for each injection) will be considered “persistent on PrEP”. Participants who do not receive all injections as scheduled will be classified as “non-persistent on PrEP”, regardless of the frequency or timing of self-reported condomless sex. Participants randomised to the oral PrEP arm will be considered “persistent on PrEP” if they attend scheduled 3-monthly visits, receive sufficient PrEP to maintain supply until the next visit, and have detectable TFV-DP levels in DBS.During the full follow-up period (18 months), persistence will be assessed as a multinomial outcome with the following categories: single modality, consistent use; multiple modalities, consistent use; single or multiple modalities, inconsistent use; and never started PrEP.Implementation co-primary outcome: This will compare the adoption (uptake when offered and choice preference of the different modalities). Uptake is defined as the proportion of participants who are offered and subsequently take PrEP (oral PrEP arm versus CAB-LA arm) during the 9-month randomised period. Choice preference will be measured as the proportion of participants who choose and use each modality (daily or ED oral PrEP or CAB-LA), captured at the start and the end of the subsequent 9-month choice period.

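### If an absent TFV-DP result counts as missing, the 10% complete-case rule drops mainly likely persisters from the oral arm only and can understate oral persistence

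*Protocol article*

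**What the plan says.** Outcomes {12} defines persistence differently in the two arms. An oral-arm man must attend the 3-monthly visits, and must also "receive sufficient PrEP to maintain supply until the next visit, and have detectable TFV-DP levels in DBS". A CAB-LA man is judged on injection dates alone, and an injection outside its window makes him non-persistent. Injections are given by site staff and entered in the case report form (Injectable PrEP, under {11c}).

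The missing-data section {20c} then says: "Participants who are lost to follow-up will be included in primary user effectiveness outcome analyses, as they will be considered non-persistent on PrEP". It leaves men discontinued for medical reasons out of this analysis and closes with: "If the proportion of participants with missing data is > 10%, then multiple imputation will be investigated; otherwise, complete case analysis only will be used". No arm-specific threshold is given.

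Dried blood spots are stored and assayed retrospectively (Collection of laboratory data). Statistical methods {20a} promises an analysis plan before database lock, with sensitivity analyses on each element of the composite outcome and on a wider visit window.

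**The concern.** The oral outcome holds only if all three elements hold, and only the third needs a laboratory result. A man who fails on attendance or supply is non-persistent whatever his assay would have shown. A lost or unusable sample therefore leaves the outcome undetermined only in men who passed the first two elements, and they are the men most likely to be persistent. The CAB-LA arm has no counterpart.

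Complete case analysis keeps every oral-arm man who failed on attendance or supply and discards some who passed. Even purely technical assay loss then lowers the observed oral proportion and moves the primary odds ratio towards CAB-LA. A threshold counted over all participants is a weak safeguard, because only half of them can have this kind of missingness.

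**Working it through.** **Scale set by the plan.** Sample size {14} plans 400 men and says that this number "will allow 80% power to detect an absolute difference of 11% in persistence between trial arms at a 5% significance level". The main scenario puts the lower arm at 80% and the other at 91%. The total is also inflated for outcomes that cannot be determined, "allowing for 20% lack of ascertainment of persistence, for example, due to medical ineligibility to receive the randomised intervention or death". Comparing 80% with 91% (two-sided 5%, pooled variance, no continuity correction) needs 160 per arm, and 320 / (1 - 0.20) = 400. The stated figure reproduces. The second scenario is 60% versus 75%. Bias should therefore be read against differences of 11 and 15 points. The 20% allowance protects precision. It does not correct bias.

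**Threshold.** If the proportion is taken over all participants, 10% of 400 is 40 men. If all 40 are in the oral arm, that is 40 / 200 = 20% of the arm, and the rule still prescribes complete case analysis.

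**Assumptions not in the article.** Loss per sample m = 3%, 5% or 7%. Number of samples that must all be available k = 1, 2 or 3. Table 1 shows blood spots at M1, M4 and M7, the oral-arm dispensing visits after M0, but the article does not say which samples count. For now, every attended and supplied man is taken to be detectable.

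**Formulas.** With P true persisters among 200 oral-arm men:
- share with an incomplete set: f = 1 - (1 - m)^k
- complete-case proportion: (P - Pf) / (200 - Pf)
- overall missingness: Pf / 400

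Example: P = 160, m = 5%, k = 3. f = 1 - 0.95^3 = 14.3%. Pf = 22.8 men. Complete case = 137.2 / 177.2 = 77.4%. Overall missingness = 22.8 / 400 = 5.7%.

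Bias in oral persistence (points):

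| True oral persistence | k | m = 3% | m = 5% | m = 7% |
|---|---|---|---|---|
| 80% | 1 | -0.5 | -0.8 | -1.2 |
| 80% | 2 | -1.0 | -1.7 | -2.4 |
| 80% | 3 | -1.5 | -2.6 | -3.7 |
| 60% | 1 | -0.7 | -1.2 | -1.8 |
| 60% | 2 | -1.5 | -2.5 | -3.5 |
| 60% | 3 | -2.2 | -3.7 | -5.3 |

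The highest overall missingness in the table is 7.8% (80%, k = 3, m = 7%), so the 10% threshold is never passed.

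**Lower detectability.** Let a be the share of the oral arm meeting the visit and supply criteria, q the share of those men who are detectable (true persistence = aq), and M the share of the arm that meets the criteria but has no assay. The complete-case proportion is (a - M)q / (1 - M), so the bias is -Mq(1 - a) / (1 - M). At 80% true persistence, m = 5% and k = 3:
- q = 0.95: a = 0.842, M = 0.842 x 0.143 = 0.120, bias -2.0 points
- q = 0.85: a = 0.941, M = 0.134, bias -0.8 points

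The table, which has q = 1, is therefore the unfavourable end.

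**At the limit of the rule.** With q = 0.95, M = 20% and true persistence of 80% in both arms, complete case gives 76.25% for oral. That is a bias of -3.75 points, an odds ratio of 1.25 favouring CAB-LA, and a type I error of about 13.7% instead of 5%. With M = 10%, the bias is -1.7 points and the type I error 6.8%.

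**Scoring a missing assay as undetectable.** The proportion becomes 80% x (1 - f). For k = 3 that is 73.0%, 68.6% or 64.3%. The direction is the same and the bias larger.

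**When the direction reverses.** Suppose observed oral persistence is 80%, 10% of the arm is missing and half of those men are persistent. The truth is 0.9 x 80% + 0.1 x 50% = 77%, so complete case is 3.0 points too high.

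**The case against.** The strongest reply is that the article never says an absent assay makes the outcome missing, how many samples are needed, or whether the 10% is counted overall or by arm. Such coding details commonly belong in an analysis plan, and one is promised. This stands as a limit: the bias is conditional on these readings, and the absent detail is not itself the fault. The complete-case rule, however, is stated, and it fits this outcome badly.

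A second reply is that the sensitivity analysis by element would expose the problem, since an analysis without the TFV-DP element keeps every attended and supplied man. That is a useful check, but it leaves the primary estimate unchanged.

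Third, the size may be small. If a single sample decides the outcome, the bias at 80% is about one point or less, against a standard error of the arm difference of about 4 points (the square root of 2 x 0.8 x 0.2 / 200). That is fair, and it is why a range is given.

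Two stronger readings are tempting. A reader might infer that the primary comparison is certain to favour CAB-LA. The documents do not support that, because men not taking tablets may decline sampling, which could weaken or reverse the effect. A reader might also infer that the threshold was chosen so that the problem goes uncorrected. Nothing in the article suggests such a purpose.

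**Conclusion.** The point holds in conditional form. The two outcome definitions and the loss-to-follow-up rule confine undetermined outcomes from missing assays to oral-arm men who met the visit and supply criteria. If those men are treated as missing, the stated rule underestimates oral persistence whenever assay loss is unrelated to drug level among them and some oral-arm men fail on attendance or supply.

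The size runs from negligible to several points, within the range tabulated above. The upper values are a material fraction of the 11- and 15-point design differences, and the lower ones are minor. Deaths may add missing outcomes in either arm, but they do not change this argument.

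**What to change.** - Do not apply the 10% complete-case rule to the TFV-DP component.
- State how a missing TFV-DP result at an attended visit is classified, and which samples count.
- At any level of missingness, multiply impute detectable or undetectable within oral-arm men who met the visit and supply criteria. Use their TFV-DP at other visits, pill count, self-reported use, regimen (daily or event-driven) and setting. In the q = 0.95 example this returns 0.842 x 0.95 = 80.0%, provided loss is unrelated to drug level given these variables.
- Report two bounds, all missing results detectable and all undetectable, together with the number of missing blood spots. In the example with 5% loss over three samples, the bounds are 160 / 200 = 80.0% and 137.2 / 200 = 68.6%.

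The cost is analysis-plan wording and modest programming with data already being collected. The downside is a slightly more complex primary analysis. It can be settled in the analysis plan before database lock.
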